### 11.4.4 Interim analyses

No interim analyses will be done.

### 11.4.5 Safety analysis

Safety endpoints (Section 10.1.1) will be reported for each study arm using summary statistics (frequencies and percentages). No statistical tests are planned for the safety endpoints.

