| Outcome(s): | All outcomes are events within 30 days (±5 days) after randomisation if not stated otherwise. Primary outcome measure Symptomatic UTI (based on clinical diagnosis) treated with antimicrobial agents. Secondary outcome measuresSymptomatic UTI (based on clinical diagnosis supported by measured bacteriuria of ≥10^5^ cfu/ml) treated with antimicrobial agents (**key secondary outcome**)  - Symptomatic cystitis (based on clinical diagnosis) - Symptomatic epididymitis (based on clinical diagnosis) - Symptomatic pyelonephritis (based on clinical diagnosis) - Symptomatic prostatitis (based on clinical diagnosis) - Symptomatic urethritis (based on clinical diagnosis) - Urosepsis (based on clinical diagnosis) - Prescription of antibiotics (for any reason) - Prescribed defined daily doses (DDD) of antibiotics (cumulative sum of DDD from randomisation to day 30) - Asymptomatic bacteriuria of ≥10^5^ cfu/ml treated with antimicrobial agents - Detection of multidrug-resistant bacteria in urine culture (3MRGN, 4MRGN) - Any *Clostridium difficile*-associated infection - Duration of catheterisation (cumulative sum of days between randomisation and end of catheterisation or day 30) - Duration of hospital stay (cumulative sum of hospital days between randomisation and day 30) - Duration of intensive care unit stay (cumulative sum of ICU days between randomisation and day 30) - Re-hospitalisation (within 30 days after randomisation) - Change of International Prostate Symptom Score (prior to randomisation and at day 30 after randomisation) - Change of Quality of life Score (prior to randomisation and at day 30 after randomisation) - All-cause mortality - Total adverse events - Total serious adverse events |
| Study design: | Pragmatic, placebo controlled, parallel arm, non-inferiority, multicentre, randomised controlled trial based on routinely collected data with blinded treating physicians, patients and outcome assessors. |

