| Statistical Considerations: | Primary analysis  The difference in the proportion of UTIs between the single-dose AP and the 3-day AP arm will be compared with the non-inferiority margin using a two-sided 95 % confidence interval calculated according to the continuity-corrected modification of Wilson’s score method. The primary analysis will be based on the intention to treat (ITT) principle. We will also conduct a per protocol (PP) analysis. We expect a very low rate of non-adherence to the treatment regimens in both groups due to the nature of the intervention. Thus we do not expect substantial differences between ITT and PP analyses. We will base our interpretation on the ITT analysis under close consideration of the results of the PP analysis when reporting and communicating the results.  **Sensitivity analysis:** In order to evaluate the robustness of imputation method the ITT analysis of the primary analysis will be repeated using inverse probability censored weighting (IPCW) methodology.  **Subgroup analysis:** The difference in the UTI proportion between the study arms will be explorative assessed with 95% confidence interval for patients treated with TURP and patients treated with GL.  Secondary analyses  Analyses of all secondary outcomes will be exploratory in nature. All estimates will be presented with 95% confidence intervals. |
| GCP Statement: | This study will be conducted in compliance with the study protocol, the current version of the Declaration of Helsinki, the ICH-GCP or ISO EN 14155 (as far as applicable) as well as all national legal and regulatory requirements. |

study summary in local language

**Einzeldosis gegenüber einer Drei-Tage-Prophylaxe während einer transurethralen Resektion der Prostata oder Greenlight Laser Vaporisation der Prostata: eine pragmatische, multizentrische, placebokontrollierte Nichtunterleigenheitsstudie.**

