## Risks / Benefits

Based on the current evidence summarised above and the improved operation techniques, we hypothesise that a shorter AP duration (single-dose, as recommended for TURP by the EAU guidelines) does not result in more complications for the patients (see also Section “11.2 Determination of Sample Size” for detailed estimations).

Intervention or control have both shown good tolerability in clinical routine already. TMP/SMX (i.e. Cotrimoxazole) is a routinely used antimicrobial substance recommended in international and in-house guidelines as AP in TURP and UTI treatment, which is well tolerable and effective. AEs due to study medication should potentially be less common in the intervention group due to the lower exposure (single-dose vs 3-day course). Main AEs are skin reactions and gastrointestinal disorders according to the Swissmedic package leaflet. Patients with a known allergy or contraindications against TMP/SMX are excluded from the study participation. In case of such a severe reaction to TMP/SMX, the administration of study medication will be stopped immediately and necessary treatment of the allergic reaction will be performed. Continuation of the surgery and application of another AP is decided by the surgeon and the anaesthetist. The placebo contains small amounts of lactose. In case of a known intolerance, patients are excluded from the study. In case of AEs, the administration will be stopped and necessary treatment of the reaction will be performed.

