## Safety Outcomes

- AEs
- SAEs

All other relevant ‘safety outcomes’ (i.e. complications) are assessed as primary or secondary outcomes.

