## Determination of Sample Size

Sample size was estimated to be able to able to show non-inferiority of single-dose AP compared to 3-day AP with at least 80 % power (1 – *β* = 0.8) at a significance level of *α* = 5 %, applying a 1:1 randomisation scheme. A drop-out rate of 10% was considered.

Determination of the non-inferiority margin $\delta$: There is no direct data available describing the effect of 3-day AP with TMP/SMX versus placebo on our primary endpoint. Based on internal data from the involved clinics, we assumed an expected UTI rate within 30 days under usual care (3-day AP) of 0.09 (9 %). A comprehensive meta-analysis (5) reported an overall risk ratio (RR) for symptomatic UTIs treated with AP versus placebo of 0.38. Applied to an expected UTI rate under 3-day AP of 9%, this corresponds to an expected (hypothetical) UTI rate under placebo of 23.68% (i.e. 0.2368 * 0.38 = 0.09) and an expected absolute treatment effect (absolute risk reduction, ARR) of 3-day AP versus placebo (M1) of 14.68% (ARR = 0.2368 – 0.09 = 0.1468). The non-inferiority margin was determined in order to preserve 70% of M1 (i.e. ARR*0.7; 10.28% on an absolute scale), which was judged a clinically important fraction. This would correspond to an absolute event rate under 1-day AP versus placebo of 13.4% (i.e. 0.2368 – 0.1028 = 0.134). Assuming an event rate of 0.09 (9 %) in both trial arms, this resulted in a non-inferiority margin $\delta$ = 4.4% (i.e. 13.4% - 9%).

In other words, when 100 patients undergoing TURP or GL would receive no treatment, 24 (i.e. 23.68%) would have a symptomatic UTI and 76 patients not. Would all these 100 be treated with 3 day AP, 9 (i.e. 9%) would still have a symptomatic UTI and 91 not. Would all these 100 be treated with a single AP (which still has 70% of the effect), approximately 13 patients would have a symptomatic UTI and 87 not.

We would consider it acceptable when approximately 4 more of 100 patients would have an UTI when bearing in mind that these 4 UTIs can be treated relatively straightforward with antibiotics and that simultaneously the use of AP can be strongly decreased in all 100 treated patients. This also very likely leads to fewer individual adverse events and resistant pathogens, and beyond this has important beneficial consequences for public heath due to lesser antibiotic resistance in general.

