### 11.4.3 Secondary Analyses

Secondary analyses will be exploratory in nature and aim to measure the ITT effect. All estimates will be presented with 95% confidence intervals.

The key secondary outcome a (Symptomatic UTI (based on clinical diagnosis supported by measured bacteriuria of ≥10^5^ cfu/ml) treated with antibiotics*)* will be analysed as described for the primary endpoint (Section 11.4.2). Results (size and direction of the effect) will be compared informally to the primary endpoint.

Secondary outcomes *b – m* (see Section 5.2) will be analysed with *generalised linear mixed models (GLMM) with binomial error distribution*, including trial arm as predictor and study centre as random effect. Estimates will be reported as odds ratios (OR).

Secondary outcomes *n – p* (see Section 5.2) will be treated as count data and analysed with *GLMM with poisson error distribution*, including trial arm as predictor and study centre as random effect. Estimates will be reported as relative effects.

Secondary outcomes *r – s* (see Section 5.2) will be analysed by means of linear mixed models (LMM), including trial arm as predictor and study centre as random effect. Estimates will be reported as absolute effects.

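### Total AEs and SAEs are secondary outcomes with confidence intervals in the synopsis but safety outcomes with per-arm counts only in section 11.4.5, so the comparative safety objective has no planned between-arm interval

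*Protocol*

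**What the plan says.** **Synopsis.** The Objective(s) row includes total and serious adverse events in the secondary objectives. The Outcome(s) row ends its list of secondary outcome measures with "Total adverse events - Total serious adverse events". The Statistical Considerations row then sets the rule for that list: "Analyses of all secondary outcomes will be exploratory in nature. All estimates will be presented with 95% confidence intervals".

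**Body, classification.** Section 5.2 has 19 secondary outcomes, and neither AEs nor SAEs are among them. They appear under Safety Outcomes in section 5, with the remark "All other relevant ‘safety outcomes’ (i.e. complications) are assessed as primary or secondary outcomes". The Safety Objectives paragraph in section 4 is worded as a comparison of the single dose with the 3-day course.

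**Body, analysis.** Section 11.4.3 repeats the interval rule ("Secondary analyses will be exploratory in nature and aim to measure the ITT effect. All estimates will be presented with 95% confidence intervals") but assigns methods only to outcomes listed in section 5.2. Section 11.4.5 says of the safety endpoints: "Safety endpoints (Section 10.1.1) will be reported for each study arm using summary statistics (frequencies and percentages". It adds: "No statistical tests are planned for the safety endpoints".

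**Use of the expected AE benefit.** The Risks / Benefits section states the expected direction: "AEs due to study medication should potentially be less common in the intervention group due to the lower exposure (single-dose vs 3-day course". Section 11.2, after deriving the margin, says of the reduced prophylaxis: "This also very likely leads to fewer individual adverse events and resistant pathogens".

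**The concern.** Someone writing the analysis tables cannot follow both rules. Under the synopsis, total AEs and total SAEs are secondary outcomes, so an effect estimate with an interval is expected. Under sections 5 and 11 they are safety outcomes and need only two columns of counts.

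The choice matters because of the design. A non-inferiority claim accepts a bounded loss on the primary outcome for gains elsewhere, and fewer adverse events is one of the gains that the protocol names. If single-dose prophylaxis is declared non-inferior, readers will want to know how large that gain is and how uncertain. Two percentages give the size of the observed difference. They do not, as printed, say which differences the data are compatible with.

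**Working it through.** **1. Does any AE quantity enter the margin, sample size or power?**

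Inputs from section 11.2: UTI rate 9% in both arms, risk ratio 0.38, 70% of the effect preserved, 80% power, two-sided 95% interval by the continuity-corrected Wilson method, 10% drop-out.

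- Placebo rate: 0.09 / 0.38 = 0.2368. M1 = 0.2368 − 0.09 = 0.1468.
- Margin: 0.30 × 0.1468 = 0.0441. The stated 4.4% is reproduced.
- Power with 1416 / 2 = 708 per arm, by exact enumeration of two binomials at 9% with the upper limit below 0.044: 80.2%. The stated 80% is reproduced.
- Recruitment: 1416 / 0.9 = 1573.3, rounded up to 1574. Reproduced.

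No AE rate appears in any of these steps.

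**2. The two rules side by side**

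| | Synopsis | Sections 5 and 11 |
| --- | --- | --- |
| Class of total AEs and SAEs | Secondary outcome | Safety outcome |
| Presentation | Exploratory estimates with 95% CI | Frequencies and percentages per arm |
| Between-arm contrast | Implied by the interval rule | None planned |
| Tests | None specified for these outcomes | None |

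**3. What is already compared**

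Under 11.4.3, secondary outcomes b to m get odds ratios with 95% intervals. They include urosepsis, antibiotic prescription, 3MRGN/4MRGN detection, *C. difficile* infection, re-hospitalisation and all-cause mortality. What remains without a contrast is total AEs (the schedule in section 9.1 places AE assessment at day 3) and the SAE total.

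**4. How wide would the missing interval be?**

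The protocol gives no AE rate, so all rates here are assumptions. With 708 per arm and a common rate p, the half-width is 1.96 × √(2p(1 − p)/708).

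| Assumed p | Half-width (points) |
| --- | --- |
| 2% | 1.5 |
| 5% | 2.3 |
| 10% | 3.1 |
| 20% | 4.2 |
| 30% | 4.8 |

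For assumed unequal rates p₁ (single dose) and p₂ (3-day), the half-width is 1.96 × √(p₁(1 − p₁)/708 + p₂(1 − p₂)/708):

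- 3% versus 5%: −2.0 ± 2.0 points.
- 5% versus 8%: −3.0 ± 2.6 points.
- 10% versus 15%: −5.0 ± 3.4 points.

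With the trial's own continuity-corrected method, about 7% versus 10% (50 and 71 men of 708) gives −3.0 points, 95% CI −6.0 to +0.1. Depending on the assumed rates, an observed reduction of 2 to 5 points may or may not exclude zero. The documents do not show which case is realistic.

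**The case against.** Descriptive safety reporting without tests is a common, deliberate choice and not in itself an error. Section 11.4.6 refers to a detailed analysis plan, which is not at hand and could add intervals to the safety tables; the decision not to test does not forbid them. This stands, and it limits the point. It does not remove the conflict: the protocol itself fixes two classes and two rules for the same outcomes, and its own safety objective is comparative.

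Three stronger readings are tempting, and the documents do not support them:

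- A reader might infer that the AE effect is never estimated. Per-arm percentages are estimates. The crude difference follows by subtraction, and with the denominators a reader can work out an interval. What is missing is a planned contrast reported with its interval.
- A reader might infer that the 4.4-point margin rests on fewer AEs. It comes from preserving 70% of M1. Fewer AEs is a supporting remark, placed after the arguments that the extra UTIs are treatable and that prophylaxis use falls, and beside the resistance argument.
- A reader might infer that the harms side of the trade goes uncompared. Much of it is modelled under 11.4.3, including the resistance outcome. Death and re-hospitalisation, two of the SAE criteria in 10.1.1, are compared there as separate outcomes.

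**Conclusion.** The inconsistency is real and should be corrected. Total AEs and SAEs are secondary outcomes with 95% intervals in the synopsis, and safety outcomes with per-arm counts in sections 5 and 11.4.5. As section 11 stands, the comparative safety objective and the AE part of the argument in 11.2 have no planned between-arm contrast with an interval.

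The consequence is limited to how the secondary trade-off is reported. The primary analysis, margin, sample size and power do not change. The half-widths of about 1.5 to 4.8 points rest on assumed common AE rates of 2% to 30% and 708 men per arm. They illustrate the precision available and are not a forecast.

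**What to change.** 1. Put total AEs and total SAEs in the same outcome class in the synopsis (Objective(s) and Outcome(s) rows) and in section 5, so that one analysis rule applies.
2. In 11.4.5, keep the per-arm frequencies and the decision not to test. Add the risk difference, single dose minus 3-day, with a 95% confidence interval for men with at least one AE (including the AEs of special interest assessed at day 3) and for men with at least one SAE. Label these intervals exploratory and unadjusted for multiplicity.

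The cost is about one sentence and a few table cells, with no new data and no change to the sample size. The small downside is a few more exploratory intervals that could be over-read, which the label addresses.

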### 11.4.6 Deviation(s) from the original statistical plan

If substantial deviations of the analysis as outlined in these sections are needed for whatever reason, the protocol will be amended. All deviations of the analysis from the protocol or from the detailed analysis plan will be listed and justified in a separate section of the final statistical report.

## Handling of missing data and drop-outs

Drop-outs will not be replaced. The number of drop-outs will be reported for each trial arm separately, indicating the reason for drop-out.

**Primary analysis:** For the ITT analysis, missing values will be imputed using multiple imputation methods. As sensitivity analysis, the analysis will be repeated using inverse probability censored weighting (IPCW) methodology (43). This approach accounts for missingness based on a logistic regression model for the probability of having a complete follow-up given past history covariates and outcomes. By using inverse weights, the impact of underrepresented subjects is inflated, so that one can observe associations that would have been observed if all subjects had stayed in the study, assuming the model is correctly specified. For the PP analysis, a complete case approach is applied where no missing values are possible.

**Secondary analyses:** Secondary analyses will be performed primarily as complete case analyses. For the key secondary endpoint [a] and secondary endpoints [r] and [s], additional (sensitivity) analyses will be performed, as described for the primary endpoint. For all other secondary endpoints, missing data will only be imputed or IPCW applied if the amount of missing values is considerable (i.e. more than 5% of values missing in one treatment group, more missing values than events in one group). This means that the number of patients may vary among analyses.

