The sample size was calculated using a re-sampling procedure. Each sample size, n_i_=1,...,111 = 800, ..., 3000, was evaluated by simulating 999 individual samples of n_i_ patients based on the assumptions described above. The difference in the observed event rates p_idAP_ – p_3dAP_ was compared with the non-inferiority margin δ, using a two-sided 95 % confidence interval, calculated using a continuity-corrected modification of Wilson’s score method (41). Non-inferiority was declared if the upper limit of this 95 % confidence interval was no larger than the non-inferiority margin δ. Figure 2 shows the relationship between the total sample size (number of patients, not including drop-outs) and the expected absolute difference in the UTI rate between the two trial arms. For an assumed event rate of 9% in both trial arms, and a δ of 4.4%, a total of 1574 patients should be recruited, in order to have 1416 evaluable patients.

[figure not shown]
**Figure 2:** Total sample size needed to show possible non-inferiority of single-dose AP to 3-day AP, depending on the absolute difference in the UTI rate. An examples is shown for an absolute difference of 0% and a power of 80%. The curves are smoothed and for illustration only.

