This is a pragmatic trial aiming to inform the practical question about how to act, i.e. we aim to compare two treatment strategies. Therefore we will use the ITT analysis as our main analysis since it is the only method to estimate the unbiased causal effect of the intention to use the two treatment strategies (i.e. the intention to begin and adhere to a 1 vs 3 day AP). However, this has the risk that the different explanatory question about the causal effect of actually using the antibiotic treatment as specified in the protocol (i.e. under the -unrealistic- assumption of perfect adherence in all patients) will be more or less biased. This explanatory question, however, can only be evaluated in a per protocol analysis under strong and unrealistic assumptions (i.e. that all post-randomisation confounder leading to non-adherence are known, measured, and well understood so that they can be accurately modelled). Within the framework of this trial it is impossible to measure all possible post-randomisation confounders (e.g. patients’ preferences and values which may lead to non-adherence or treatment switch). Nevertheless, acknowledging these issues, we will use a PP analysis to estimate this per protocol effect. We assume that in this clinical situation only very few patients will be “non-adherent” due to the very short treatment period and that missing data is rarely (if ever) associated with the treatment allocation (i.e. missing completely at random) leading to small differences between the two estimates. In our publications (and other study reports), we will report the results of both analyses, discuss any differences and carefully describe the conceptual differences of both analyses

**Sensitivity analysis:** In order to evaluate the robustness of the imputation method the ITT analysis of the primary analysis will be repeated using inverse probability censored weighting (IPCW) methodology (details see Section 11.5).

**Subgroup analysis:** The difference in the UTI rate between the study arms will be estimated and reported with 95% confidence interval separately for patients treated with TURP and patients treated with GL. No other subgroups are pre-specified.

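### The only stated check on missing primary outcomes, IPCW, shares the missing-at-random assumption of the multiple imputation, so it cannot show whether outcome-related missingness affected the non-inferiority claim

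*Protocol*

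**What the plan says.** Section 11.5 imputes missing primary outcomes for the ITT analysis by multiple imputation. As the sensitivity analysis, "the analysis will be repeated using inverse probability censored weighting (IPCW) methodology", with weights from a logistic model for complete follow-up fitted to observed covariates and outcomes. Section 11.4.2 gives the purpose: "In order to evaluate the robustness of the imputation method". The per-protocol analysis uses complete cases. The protocol states no analysis that lets missing patients differ from observed patients with the same recorded history.

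Section 11.4.2 warns that attrition can dilute a difference and lead to a false non-inferiority claim under ITT. It then explains why ITT and per-protocol results should be close, on the assumption that "missing data is rarely (if ever) associated with the treatment allocation (i.e. missing completely at random".

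Section 11.2 plans for 10% drop-out: with 9% events in both arms "and a δ of 4.4%, a total of 1574 patients should be recruited, in order to have 1416 evaluable patients".

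**The concern.** Multiple imputation as described, with no shift or pattern-mixture term, and IPCW both require missingness to depend on observed data only. If it depends on whether the man had a UTI, beyond what his recorded history predicts, the two are biased in the same direction and agree with each other. Agreement could then be reported as robustness although the assumption that matters was never varied. The complete-case per-protocol analysis needs an assumption at least as strong, so it does not fill the gap.

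The sentence on missing completely at random has a separate fault. Missingness can be unrelated to arm and still depend on the outcome. If men with a UTI are lost more often, equally in both arms, missingness is close to unrelated to arm, yet the observed difference is smaller than the true one.

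At stake is the risk that section 11.4.2 itself raises: a non-inferiority claim produced partly by missing data, with no stated analysis able to show it.

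**Working it through.** **Inputs (section 11.2).** Margin 4.4 points; 9% in both arms; "applying a 1:1 randomisation scheme"; decision "using a two-sided 95 % confidence interval, calculated using a continuity-corrected modification of" Wilson's score method. Per arm: 1,574/2 = 787 recruited, 1,416/2 = 708 evaluable, 787 − 708 = 79 missing.

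**1. The plan's own figure.** The upper limit is p1 − p2 + √[(u1 − p1)² + (p2 − l2)²], where u1 and l2 are continuity-corrected Wilson limits for the single arms. Exact binomial enumeration at 708 per arm and 9% v 9% gives power 80.2%, and 1,416/0.9 rounds up to 1,574. The stated sample size reproduces. With the true difference at the margin (13.4% v 9%), the probability of a false claim is 2.2%.

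**2. Do the two methods separate?** A simulation with 787 per arm, 13.4% v 9% and about 10% missing compared IPCW with regression imputation (the expectation of multiple imputation) on the same covariate. It used a Wald interval and one binary covariate unrelated to the outcome.

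| Assumed missingness | IPCW estimate | Imputation estimate |
|---|---|---|
| Random, 10% in both arms | 4.4 points | 4.4 points |
| Both arms: events 30%, non-events 8% | 3.5 points | 3.5 points |
| Single-dose: events 25%, non-events 7.7%; control random 10% | 2.2 points | 2.2 points |

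The estimates agree whether or not they are right. Covariates that predict the outcome would reduce the bias, but for both methods alike.

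**3. Direction and size, same mechanism in both arms.** Let a man without a UTI be missing with probability m and a man with a UTI with probability k·m. For overall missingness d, m = d / [1 + (k − 1)(0.134 + 0.09)/2]. The observed rate is p(1 − km) / [1 − m(1 + (k − 1)p)].

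For k = 2 and d = 0.10: m = 0.10/1.112 = 0.0899. Single-dose: 0.134 × 0.8201/0.8980 = 12.2%. Control: 0.09 × 0.8201/0.9020 = 8.2%. The difference is 4.05 points before rounding.

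False-claim probabilities, with 708 evaluable per arm throughout:

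| Missing (d) | k | Observed difference | False claim |
|---|---|---|---|
| any | 1 | 4.40 | 2.2% |
| 10% | 2 | 4.05 | 3.5% |
| 10% | 3 | 3.77 | 5.3% |
| 10% | 0.5 | 4.60 | 1.7% |
| 5% | 2 | 4.24 | 2.7% |
| 2% | 2 | 4.34 | 2.4% |

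**4. Tipping point.** Take 64/708 observed in each arm (0.09 × 708 = 63.7). On observed data alone the upper limit is 3.1%, so non-inferiority is declared. Give the 79 missing controls 7 events (0.09 × 79 = 7.1), so control is 71/787. With 17 events among the 79 missing single-dose men the upper limit is 4.30%. With 18 of 79 (23%) it is 4.44%, and the claim is lost. From the weakest observed result that still passes (72/708 v 64/708), 10 of 79 (13%) is enough.

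With 40 missing per arm and equal observed rates, 15 of 40 (38%) is needed; with 16 missing, 12 of 16 (75%).

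The values of k, the missingness levels below 10% and the event rates among missing men are assumptions. The protocol gives none of them.

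**The case against.** The strongest reply concerns direction and size. A reader might infer that any outcome-related missingness favours non-inferiority. The arithmetic does not support that: at k = 0.5 in both arms the difference widens and the false-claim probability falls. The protocol gives some reason to expect that direction, since in-hospital UTIs and re-hospitalisations are read from the hospital information system (section 9.2.1) and a treated UTI leaves a prescriber to contact. On the other side, men may refuse contact for themselves and their physician (Criteria for withdrawal / discontinuation of participants), and UTIs after discharge are found mainly by asking the patient. The direction is therefore open.

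A reader might also take 10% as the expected share of missing primary outcomes. It is a sample-size allowance. Re-scheduling, telephone contact and physician contact (sections 9.2.1 and 9.3.6) and continued use of routine data (section 9.2.5) should reduce it, and at 2–5% the effect is small. Strong missingness confined to one arm would do more harm, but nothing in this blinded design supports assuming it.

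It is also fair that IPCW does what it is stated to do, since it checks for a misspecified imputation model, and that the primary analysis does not rely on missingness being completely at random. Both points stand. A SAP that is not shown may add further analyses, so the gap can be asserted only for the protocol. That does not answer the point: the protocol itself chooses the sensitivity analysis and states the mistaken rationale.

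**Conclusion.** The point holds in limited form. The one sensitivity analysis that the protocol states cannot detect missingness that depends on the unobserved UTI, and the equation of independence from arm with missing completely at random is wrong as written.

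The size depends on how much is missing and in which direction. At 10% missing, with men with a UTI two to three times as likely to be missing in both arms, the false-claim probability is 3.5–5.3% against 2.2%. At 2–5% and twofold it is 2.4–2.7%, which is little change. The bias runs towards non-inferiority only if men with a UTI are lost more often, in both arms or mainly in the single-dose arm. A claim that missing data will produce non-inferiority here, or that IPCW is worthless, goes beyond what the protocol supports. The addition is worth making because it is cheap and because section 11.4.2 names this risk itself.

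**What to change.** In sections 11.4.2 and 11.5, keep IPCW as the check on the imputation model. Add a delta-adjusted (tipping-point) multiple imputation of the primary outcome: first raise the imputed UTI odds or risk among missing single-dose men with control left at missing at random, then shift both arms together. Report the shift at which the upper 95% limit reaches 4.4 points, so that readers can judge whether it is plausible.

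In section 11.4.2, reword the assumption so that it says only that missingness is expected to be rare and unrelated to arm, and remove the equation with missing completely at random.

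The cost is one further analysis on an imputation model already planned, with no new data. The downside is that a claim close to the margin may be shown to be fragile.
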